## Abstract

**Introduction:** Physical activity is associated with many physiological and psychological health benefits across the lifespan. Children with a chronic disease often have lower levels of daily physical activity, and a decreased exercise capacity compared to healthy peers. In order to learn more about limitations for physical activity, we investigate children with four different chronic diseases: children with a Fontan circulation, children with Broncho Pulmonary Dysplasia (BPD), Pompe disease and inflammatory bowel disease (IBD). Each of these diseases is likely to interfere with physical activity in a different way. Knowing the specific limitations for physical activity would make it possible to target these, and increase physical activity by a personalized intervention. The aim of this study is to first investigate limitations for physical activity in children with various chronic diseases. Secondly, to measure the effects of a tailored exercise intervention, possibly including a personalized dietary advice and/or psychological counseling, on exercise capacity, endurance, quality of life, fatigue, fear for exercise, safety, muscle strength, physical activity levels, energy balance, and body composition.

**Methods and Analysis:** This randomized crossover trial will aim to include 72 children, aged 6–18 years, with one of the following diagnosis: a Fontan circulation, BPD, Pompe disease and IBD. Eligible patients will participate in the 12-week tailored exercise intervention and are either randomized to start with a control period or start with the intervention. The tailored 12-week exercise interventions, possibly including a personalized dietary advice and/or psychological counseling, will be designed based on the found limitations for physical activity in each disease group during baseline measurements by the Rotterdam Exercise Team. Effects of the tailored training interventions will be measured on the following endpoints: exercise capacity (measured by cardiopulmonary exercise test), endurance, physical activity levels, muscle strength, quality of life, fatigue, fear for exercise, disease activity, cardiac function (in children with a Fontan circulation), energy balance, and body composition.

**Ethics and Dissemination:** Conducted according to the Declaration of Helsinki and Good Clinical Practice. Medical-ethical approval was obtained.

**Trial Registration Number:** NL8181, https://www.trialregister.nl/trial/8181.

## Introduction

Physical activity is of vital importance for the healthy development of children (1, 2). It is associated with many physiological and psychological health benefits across the lifespan. Many children with a chronic disease have lower levels of daily physical activity and lower exercise capacity compared to healthy peers (1). Children with a chronic disease may face obstacles that negatively impact physical activity or sports participation (3, 4). Some conditions may directly influence exercise capacity causing a circulatory, ventilator or peripheral limitation, where others may influence physical activity indirectly due to disease related symptoms like fatigue, dyspnea, diarrhea etc. Even more, sometimes parents are scared to let their sick child participate in sports activities (3). In order to unravel the influence of these burdens on physical activity, we investigate children with four different chronic diseases: children with a Fontan circulation, children with Broncho Pulmonary Dysplasia (BPD), Pompe disease and inflammatory bowel disease (IBD), which all are likely to interfere with physical activity in a different way. Knowing the specific limitations for physical activity might make it possible to target these limitations, and increase physical activity by a tailored intervention. Conceivably, leading to a positive impact on both physiological and psychological health in these children.

Cardiovascular diseases may directly impact exercise capacity causing a circulatory limitation. In children, congenital heart defects are the most frequent type of cardiovascular disease (5). Children with a severe congenital heart defect (like two of the most common: Tetralogy of Fallot or an univentriculair heart) often have impaired exercise capacity and are less physically active compared to healthy peers (5, 6). Several studies have investigated effects of aerobic exercise training in these children, in order to increase exercise capacity and quality of life (7). Duppen et al. showed beneficial effects of aerobic exercise training in children with a Tetralogy of Fallot, but not in children with an univentricular heart threated with a Fontan procedure (6). Strength training, focusing on lower limbs, has been suggested to be more effective in patients with a Fontan circulation due to their different physiology compared to those with a normal (biventricular) heart (8). Despite a very small study in adult patients, this kind of training has never been researched before.

Pulmonary diseases are likely to influence exercise capacity by ventilatory limitation (9). BPD is a common respiratory complication of preterm born children and associated with long-term respiratory problems, including a decreased lung function and decreased exercise capacity (9). Adult survivors with BPD have lower sports participation and physical activity levels compared to healthy peers (10). Although physical exercise training has been proven very effective in various other chronic lung diseases as cystic fibrosis in children and COPD in adults, only one study exists investigating effects of a 4-week exercise program in patients with BPD (11, 12). After 4 weeks lung function improved in these children. However the mechanism of impact on exercise capacity remains unclear, since exercise capacity was not measured in this small study.

Musculoskeletal disorders might cause a peripheral limitation directly influencing exercise capacity. Pompe disease is a lysosomal storage disease caused by a deficiency of the enzyme acid-α-glucosidase, causing a progressive generalized myopathy (13). Treatment with enzyme replacement therapy (ERT) has shown to improve motor function and survival. Despite ERT treatment, many Pompe disease patients eventually become ventilator or wheelchair dependent. It is known that patients with Pompe disease has a decreased exercise capacity which is not caused by impaired skeletal muscle glycogenetic capacity but rather by muscle weakness and wasting (14). A study by van den Berg et al. published in 2015 showed that exercise training in adult patients with late onset Pompe disease might be a safe and effective adjuvant therapy for ERT (15). Research investigating physical training in pediatric Pompe disease patients, and specifically the more severe form Classic Infantile Pompe disease, has not been done before.

Inflammatory bowel disease (IBD), including both ulcerative colitis (UC) and Crohn's disease (CD), is a chronic inflammatory diseases of the gastrointestinal tract, and is one of the most common auto-immune diseases in children (16). IBD is characterized by periods of remission punctuated with relapse. Current standard of care for pediatric IBD patients includes a combination of pharmacotherapy, nutritional support or treatment, and in some cases surgical intervention (17). Despite treatment options, quality of life often remains reduced in children with IBD compared to healthy peers (18). Also, previous studies showed that patients with IBD often have reduced levels of physical activity and a lower exercise capacity compared to peers (19). IBD patients often experience barriers to exercise due to IBD related symptoms such as fatigue, diarrhea and even fear of symptom exacerbation. Evidence supporting that exercise can improve the course of various auto-immune diseases in adult patients is growing (20). An explanation is that physical activity promotes the release of IL-6 from muscles, a myokine possibly causing ant-inflammatory responses. Small studies in adult IBD patients have shown positive effects of exercise with reports of increased exercise capacity, improved fatigue and quality of life and even positive effects on the clinical course of disease (21). Studies investigating the effects of physical activity on inflammation, physical and psychological health in children with IBD and other auto-immune diseases are very limited.

The aim of the exercise study is first to investigate whether children with these chronic diseases are limited in their physical functioning and to unravel the disease specific burden to physical activity. Secondly, to measure the effects of a tailored exercise intervention (possibly including dietary advice and/or psychological counseling) on exercise capacity, endurance, quality of life, fatigue, fear for exercise, safety, muscle strength, physical activity levels, energy balance, and body composition.

## Methods and Analysis

### Study Design

This study is a prospective single-center randomized cross-over controlled trial. Eligible patients will participate in the 12-week tailored exercise intervention and are either randomized to start with a control period or start with the intervention. The tailored 12-week exercise interventions will be designed based on the found limitations for physical activity in each disease group during baseline measurements and previously published studies. Effects of the tailored exercise interventions will be measured on the following endpoints: exercise capacity (measured by cardiopulmonary exercise test), endurance, physical activity levels, muscle strength, quality of life, fatigue, fear for exercise, disease activity, cardiac function (in children with a Fontan circulation), energy balance, and body composition. Figure 1 shows the study design, visits, and measurements. The study includes two identical visits and a follow-up moment for group A and three identical visits for group B. Each visit consists of two assessment days with at least 3 days and maximal 7 days in between. All measurements will take place at the Erasmus MC—Sophia Children's hospital, the Netherlands. The study will be performed in accordance with the Declaration of Helsinki. It was approved by the local Ethics Committee of Erasmus MC Medical Centre (NL.70912.078.19) and registered at www.trialregister.nl as Trial NL8181.

**Figure 1 F1:**
[figure not shown]
Study design, visits, and measurements. PCDAI, Pediatric Crohn's Disease Activity Index; PUCAI, Pediatric Ulcerative Colitis Activity Index; CPET, cardiopulmonary exercise testing; PedsQol, pediatric quality of life questionnaire; MFS, multifatigue scale; CR and PR, child and parent reports; CHQ, child health questionnaire; 6MWT, 6-minute walking test; BODPOD, body composition measurement; MRI, magnetic resonance imaging; IBD, inflammatory bowel disease; STST, sit to stand test; QMFT, quality motor function test.

### Study Population

In total 72 children will be included in this trial. Children were eligible for inclusion when aged 6–18 years old and diagnosed with one of the following four diseases:

Fontan circulation: Patients with a proven univentricular heart using echocardiogram who underwent the Fontan procedure.BPD: Children had to have (1) persistent oxygen demand and/or by means of an oxygen reduction test and (2) abnormalities (hyperinflation, fine reticular lung image and/or atelectasis) on the X-ray of the lungs in a newborn in what would have been week 36 of pregnancy.Pompe disease: Confirmed deficiency of α-glucosidase in leucocytes or lymphocytes, fibroblasts or muscle and/or two pathogenic GAA variants in trans (www.pompevariantdatabase.nl) (22).IBD: Confirmed by ileocoloscopy and esophagogastroduodenoscopy with histology on multiple mucosal biopsies.

Exclusion criteria were:

Children <120 cm, as the cardiopulmonary exercise test cannot be executed.Physical inability to perform a cardiopulmonary exercise test (CPET).Participation in organized exercise training programs in a research setting.Medical contra-indications for exercise.

### Randomization

Randomization will be performed in blocks of 4,6 using Castor. All children will be randomized in group A or group B. Group A will start with the tailored intervention after a control period of 6 weeks. Group B will start the tailored intervention immediately after the first measurement moment. Group A serves as controls for the whole group (with a 2:1 ratio) as group A does not have a washout period. Blinding of participants and physiotherapists to allocation is not possible due to the nature of the intervention.

### Sample Size Calculation

The power calculation is based on the primary study outcome of change in peak VO_2_ after the tailored intervention. As reported peak VO_2_ in literature is different for every patient group, the group size needed to observe an increase in peak VO_2_ of at least 5%, which is clinically relevant, is different for each diagnose.

Fontan group size calculation: Previous studies show that children with a single-chamber heart have a Peak VO_2_ of 27 ml/kg/min (23). The difference of a 5% increase in Peak VO_2_ can be observed with a power of 80% and an alpha of 0.05 in 21 children with a unicameral heart assuming a standard deviation of 2.19 VO_2_/kg (24).

*BPD Group Size Calculation*: Average children with BPD have a VO_2max_ of 39 ml/kg/min (25). An improvement in VO_2max_ of at least 5% is considered clinically relevant. The difference of an increase in VO_2max_ of 5% can be observed with a power of 80% and an alpha of 0.05 in a sample of 10 children with BPD, assuming a standard deviation of 2.19 VO_2_/kg (24).

*Pompe Group Size Calculation*: The only previous study investigating exercise capacity in children with Pompe disease includes five patients and shows that children with Pompe have a PeakVO_2_ between 11.1 and 40.2 ml/kg/min, with a 75%ile of 37.7 ml/kg/min (14). We have chosen to use the 75%ile to calculate the group size, as we think this value of PeakVO_2_ is closest to the PeakVO_2_ of our own Pompe children population. An improvement in PeakVO_2_ of at least 5% is considered clinically relevant. The difference of a 5% increase in PeakVO_2_ can be observed with a power of 80% and an alpha of 0.05 at a number of 10 children with Pompe disease assuming a standard deviation of 2.19 VO_2_/kg (24).

*IBD Group Size Calculation*: In previous studies, untrained children with IBD had an average peak VO_2_ of 36 ml/kg/min (19). Twelve IBD patients will be needed in order to observe an increase in peak VO_2_ of at least 5%, which is clinically relevant, with a power of 80% and an alpha of 0.05 based on a standard deviation of 2.19 VO_2_/kg (24).

Anticipated on a dropout rate of 30–40% at 16 patients with IBD, 14 patients with Pompe disease, 28 patients with a Fontan circulation and 14 patient with PBD will be included.

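### The 80% power stated for the Pompe group rests on an unsupported upper-quartile baseline from five children, and 10 completers fall slightly short of 80% even at that value

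*Protocol article*

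**What the plan says.** All in the protocol article.

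- **Sample Size Calculation, source:** "The only previous study investigating exercise capacity in children with Pompe disease includes five patients". Values run from 11.1 to 40.2 ml/kg/min, with a 75th percentile of 37.7.
- **Choice and reason:** "We have chosen to use the 75%ile to calculate the group size", followed in the same sentence by "as we think this value of PeakVO_2_ is closest to the PeakVO_2_ of our own Pompe children population".
- **Claim:** a 5% rise "can be observed with a power of 80% and an alpha of 0.05 at a number of 10 children with Pompe disease", with an SD of 2.19. The same SD is used for all four diagnoses.
- **Other groups:** the planning values are 27 (Fontan), 39 (BPD) and 36 (IBD), each presented as an average or typical value. Only Pompe uses an upper quartile.
- **Recruitment:** 14 Pompe children, allowing for 30–40% dropout.
- **Study Population:** the Pompe criterion is diagnostic: "Confirmed deficiency of α-glucosidase in leucocytes or lymphocytes, fibroblasts or muscle and/or two pathogenic GAA variants in trans". The general limits are age 6–18, height of at least 120 cm, ability to perform a CPET, no medical contraindication to exercise, and no concurrent organised training in a research setting.
- **Statistical Analysis:** before–after differences are tested with a paired t-test when normally distributed.

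**The concern.** The effect to be detected is a percentage of baseline while the SD is a fixed number. Every unit added to the assumed baseline therefore enlarges the absolute effect and lowers the required number. An upper quartile of five children is a favourable input, and it is used for one group only.

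The document gives no peak VO2 data from the centre to support it. The Introduction describes Pompe disease as a progressive myopathy with reduced exercise capacity, yet the Pompe planning value lies above the one for IBD. If the enrolled children average less than 37.7, the 80% figure overstates what the group can show, and a non-significant Pompe result would carry less information about a 5% gain than the protocol implies.

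**Working it through.** **Inputs (Sample Size Calculation):** SD 2.19; alpha 0.05; power 80%; effect d = 0.05 × baseline. The article states neither the formula nor the sidedness, so both are inferred by reproducing the other groups.

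**Step 1: reproduce the stated sizes.** Two-sided paired (one-sample) normal formula:

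n = [2.19 × (1.960 + 0.8416) / d]² = (6.135 / d)²

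| Group | Baseline | d | n computed | n stated |
|---|---|---|---|---|
| Fontan | 27 | 1.35 | 20.7 → 21 | 21 |
| BPD | 39 | 1.95 | 9.9 → 10 | 10 |
| IBD | 36 | 1.80 | 11.6 → 12 | 12 |
| Pompe | 37.7 | 1.885 | 10.6 → 11 | 10 |

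Three groups match exactly. Pompe is one child short, which suggests rounding down. For Pompe, a one-sided version gives 9, an exact paired t-test 13, and a two-sample formula 22 per arm.

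**Step 2: power of 10 completers at the protocol's own value.** Normal: Φ(1.885 × √10 / 2.19 − 1.960) = Φ(0.762) = 78%. Noncentral t with 9 degrees of freedom: 68%.

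**Step 3: highest mean the cited series can have.** Take five values with minimum 11.1 and maximum 40.2.

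- If the 75th percentile is the fourth ordered value, the second to fourth values are at most 37.7. The mean is at most (11.1 + 3 × 37.7 + 40.2)/5 = 32.9.
- If it is interpolated midway between the fourth and fifth values, the fourth is 2 × 37.7 − 40.2 = 35.2. The mean is at most (11.1 + 3 × 35.2 + 40.2)/5 = 31.4.

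So 37.7 lies above any mean the source can have.

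**Step 4: sensitivity, SD held at 2.19.** Each cell gives the normal formula, then the paired t-test.

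| Baseline | n for 80% | Power, 10 completers | Power, 14 completers |
|---|---|---|---|
| 37.7 (protocol) | 11 / 13 | 78% / 68% | 90% / 85% |
| 36 | 12 / 14 | 74% / 64% | 87% / 81% |
| 32.9 (highest possible source mean) | 14 / 16 | 66% / 56% | 80% / 74% |
| 30 (illustrative) | 17 / 19 | 58% / 49% | 73% / 66% |
| 25.65 (midpoint of the range) | 23 / 25 | 46% / 38% | 59% / 53% |

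**Step 5: how many complete.** 14 × 0.70 = 9.8 and 14 × 0.60 = 8.4, so about 8 to 10. The 14-completer column is reached only without dropout.

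**Step 6: detectable change at 80% power, normal formula.** With 10 completers it is 6.135/√10 = 1.94 ml/kg/min: 5.1% of 37.7, 5.9% of 32.9 and 7.6% of 25.65. With 14 it is 6.135/√14 = 1.64: 4.3%, 5.0% and 6.4%.

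**Step 7: if the SD scaled with baseline.** With SD = c × baseline, n = [c × 2.8016 / 0.05]². Baseline cancels and n does not change. The loss in step 4 therefore depends on a fixed SD, which the protocol itself assumes for baselines from 27 to 39. The 25.65 row extends that assumption slightly below this range.

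**The case against.** The strongest reply is that the choice is disclosed and reasoned. The trial is single-centre, so the centre's own Pompe children are the recruitment pool, and the investigators say 37.7 is closest to them. The limits on height, CPET ability and contraindications may well remove the least fit children. A condensed article may also leave supporting data to the full protocol.

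Much of this stands. A reader might infer that the 80% power describes a fitter population than the criteria select. The document does not support that: it gives no peak VO2 for the centre's eligible Pompe children in either direction. The Introduction's remark that training in "specifically the more severe form Classic Infantile Pompe disease, has not been done before" identifies a research gap and does not describe who will be enrolled. The comparison with IBD and BPD values crosses different sources.

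A reader might also take 46–50% as the real power. Those figures come from the midpoint of the range, which one child at 11.1 pulls down, and from the Fontan baseline of 27. The document offers neither as a Pompe mean. The three quoted statistics even allow a source median as high as 37.7.

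Three things remain. The reason given is a belief without figures. CPET ability cannot by itself secure 37.7, because the child at 11.1 also had a measured peak VO2. And the shortfall with 10 completers at 37.7 does not depend on which baseline is right.

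**Conclusion.** The concern holds as an unsupported, favourable planning input behind a stated power figure.

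- At the protocol's own value, 10 completers give 78% (68% by the planned paired t-test), not 80%. This small shortfall is separate from the percentile choice.
- At the highest mean the cited series allows, about 32.9, 10 completers give 66% (56%) and 14 are needed. All 14 recruits would give 80% (74%), but the planned dropout leaves about 8 to 10.
- Lower baselines reduce power further. How far is unknown, because the document gives no central value for Pompe children.

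These figures assume a two-sided test, 2.19 as the SD of the within-child change, and no change in that SD at lower baselines. If the SD fell in proportion to baseline, the percentile choice would not affect the required number. That the enrolled children will in fact be less fit is not shown.

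**What to change.** Keep the 14 recruits and correct the claim in one of two ways:

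1. Report the centre's own peak VO2 data for eligible Pompe children in support of 37.7, and give the power of 10 completers at that value as computed.
2. Restate power and detectable percentage change over a range of baselines that includes a central value, for example 25–38 ml/kg/min, for the expected number of completers.

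In either case, state the formula, the sidedness and that the SD is held fixed. Label the Pompe result as estimation, reported with a confidence interval, if power is below 80%.

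The cost is a short rewording and one recalculated line. No extra patients or design change are needed, though the stated Pompe power will look less favourable.

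### Enrolment of 28/14/14/16 absorbs 25–29% dropout, not the stated 30–40%; the shortfall is small at 30% and material at 40%

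*Protocol article*

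**What the plan says.** All the figures are in the protocol article, under Sample Size Calculation and Study Population.

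- The target is set separately for each disease as "the group size needed to observe an increase in peak VO_2_ of at least 5%, which is clinically relevant". Power is 80%, alpha 0.05, and the standard deviation is 2.19 ml/kg/min in every group.
- The Fontan requirement reads "can be observed with a power of 80% and an alpha of 0.05 in 21 children with a unicameral heart". The other requirements are 10 (BPD), 10 (Pompe) and 12 (IBD), which makes 53 in total.
- Enrolment follows: "Anticipated on a dropout rate of 30–40% at 16 patients with IBD, 14 patients with Pompe disease, 28 patients with a Fontan circulation". The sentence goes on to give 14 for BPD (printed as PBD).
- Study Population gives the same total: "In total 72 children will be included in this trial".

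No formula is given for moving from required to enrolled numbers. Statistical Analysis specifies a per protocol analysis with paired tests, and multiple imputation of missing outcomes only where possible.

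**The concern.** Required number, dropout rate and enrolment stand next to each other in one section, so any two of them fix the third. Enrolment exceeds the requirement by a third (Fontan, IBD) or by 40% (BPD, Pompe). Those look like the two ends of a 30–40% allowance, but they are percentages of the required number. A dropout rate applies to the number enrolled, which is a larger base, so the same margin covers a smaller rate.

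What is at stake is the 80% power for change in peak VO2, which the plan claims for each disease on its own. If dropout turns out as the plan expects, each group is analysed with fewer children than the plan says it needs. A reader of a null result in one disease would then credit the trial with more sensitivity than it had.

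**Working it through.** **Inputs (Sample Size Calculation).** Baseline peak VO2 is 27 (Fontan), 39 (BPD), 37.7 (Pompe, 75th percentile) and 36 (IBD) ml/kg/min. The target is a 5% increase, SD is 2.19, alpha 0.05 and power 80%. Sidedness is not stated; I assume two-sided because that comes closest to the stated group sizes.

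**Step 1: reproduce the required numbers.** One-sample (paired) normal approximation: n = (2.19 × (1.960 + 0.842) / δ)², with δ = 0.05 × baseline.

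| Group | δ | δ/SD | n computed | n stated |
|---|---|---|---|---|
| Fontan | 1.35 | 0.616 | 20.7 | 21 |
| BPD | 1.95 | 0.890 | 9.9 | 10 |
| Pompe | 1.885 | 0.861 | 10.6 | 10 |
| IBD | 1.80 | 0.822 | 11.6 | 12 |

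Three groups match after rounding up. Pompe would round up to 11, one more than stated.

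**Step 2: dropout that the enrolment tolerates**, 1 − required/enrolled:
- Fontan: 1 − 21/28 = 25.0%
- IBD: 1 − 12/16 = 25.0%
- BPD and Pompe: 1 − 10/14 = 28.6%

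**Step 3: where the enrolment numbers could come from.** 28/21 = 1.333, 16/12 = 1.333 and 14/10 = 1.40. All four equal required × (1 + d) with d between 33% and 40%.

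**Step 4: enrolment needed**, required/(1 − d), rounded up:

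| Dropout | Fontan | BPD | Pompe | IBD | Total |
|---|---|---|---|---|---|
| 30% | 30 | 15 | 15 | 18 | 78 |
| 40% | 35 | 17 | 17 | 20 | 89 |
| Planned | 28 | 14 | 14 | 16 | 72 |

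At 30% the plan is 2/1/1/2 children short, 6 in total. At 40% it is 7/3/3/4 short, 17 in total.

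**Step 5: expected completers and power.** Expected completers are enrolled × (1 − d), not rounded. Power is Φ((δ/SD) × √completers − 1.960).

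| Group | Power at required n | Completers, 30% | Power, 30% | Completers, 40% | Power, 40% |
|---|---|---|---|---|---|
| Fontan | 81% (n = 21) | 19.6 | 78% | 16.8 | 71% |
| BPD | 80% (n = 10) | 9.8 | 80% | 8.4 | 73% |
| Pompe | 78% (n = 10) | 9.8 | 77% | 8.4 | 70% |
| IBD | 81% (n = 12) | 11.2 | 79% | 9.6 | 72% |

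Worked example, Fontan at 40%: 0.616 × √16.8 = 2.527; 2.527 − 1.960 = 0.567; Φ(0.567) = 71%.

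Total expected completers are 72 × 0.7 = 50.4 and 72 × 0.6 = 43.2, against 53 required.

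**Step 6: the paired t-test, for context.** With the noncentral t distribution, power at the full stated 21/10/10/12 is already 77/71/68/74%. That gap from 80% comes mainly from sizing with a normal approximation and has nothing to do with dropout. At 40% dropout, with completers rounded down to 16/8/8/9, it is about 64/58/55/58%. Only the difference between these two rows can be put down to lost children, and the rounding down adds to it.

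**The case against.** **The shortfall at 30% is trivial.** Largely true. BPD and Pompe miss by 0.2 expected completers, and four losses out of 14 still leave 10. Fontan misses by 1.4 and IBD by 0.8. A reader might infer that power is clearly lost across the whole stated range. The figures do not support that: at 30% dropout costs about 1 to 3 points of power, and larger losses appear only if completers are rounded down or t-test figures are compared with 80%. The objection does not reach the 40% end, which the plan also names.

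**The range may be an add-on margin and not a loss rate.** The ratios in Step 3 fit this well. Since no formula is given, one can say only that the numbers are consistent with multiplication, not that the wrong formula was used. But the text calls the range a dropout rate, so on this reading the sentence still needs correcting.

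**Imputation will recover the losses.** It is planned only where possible, alongside a per protocol analysis. It does not restore the lost information, and the sample size section does not rely on it.

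**The detail belongs in the full protocol.** This would answer an omission. Here the article prints three figures that disagree.

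**Conclusion.** The point holds as a contradiction between printed figures. Enrolment of 28/14/14/16 tolerates 25% dropout (Fontan, IBD) or 28.6% (BPD, Pompe), and no group covers even the low end of the stated range. This needs only the stated required and enrolled numbers.

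The consequence for power depends on where in the range dropout falls: 78/80/77/79% at 30%, which is minor, and 71/73/70/72% at 40%, a fall of about 7 to 9 points from power at the stated n. These figures assume a two-sided test, the normal approximation that comes closest to the plan's group sizes, and loss of every dropout from the analysis. Pompe starts at 78% because its 10 is one child below the computed requirement, so its gap from 80% is not all due to dropout.

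A reader might also infer from t-test power of 55–64% at 40% that dropout alone removes that much. It does not, because the t-test baseline with no shortfall is 77/71/68/74%.

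This should be fixed. It changes a stated property of the sample size, but no analysis and no aspect of conduct.

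**What to change.** Keep 72 and amend Sample Size Calculation in two sentences:

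1. Replace the 30–40% statement with the dropout that the enrolment tolerates: 25% for Fontan and IBD, 29% for BPD and Pompe.
2. Say whether 30–40% is still the expected dropout. If it is, give 78/80/77/79% at 30% and 71/73/70/72% at 40% (Fontan/BPD/Pompe/IBD) as the expected power in place of 80%. If t-test power is reported instead, show it beside its value at 21/10/10/12.

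The cost is a less favourable power statement. No additional children and no change to the design or analysis are needed. Covering the stated range by enrolment instead would take 6 more children at 30% and 17 more at 40%.
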